### Assessment criteria

These criteria were measured for a 6-month period (May 2–November 2, 2014) preceding the intervention year and will be measured again in the 6 months following the end of the intervention, corresponding to the same months of the year.

The primary assessment criterion is the NMIC rate.

We conducted a literature review to discern the diagnostic reasoning underlying evidence-based indications for caesareans. The four main indications for caesareans in Burkina Faso are: previous caesarean, prolonged/obstructed labour, pre-eclampsia, and acute foetal distress. In the 22 participating hospitals in the pre-intervention study, these four indications accounted for 76 % of all caesareans performed. The relevant references [47–70] were consulted and used to generate a provisional list of good practice criteria. Preference was given to evidence obtained through randomized controlled trials, considered the most rigorous. The provisional list of criteria was sent to 16 international and national experts (gynecologist-obstetricians, midwives, and a public health physician, see Additional file 10). The experts gave their opinions on the relevance of each criterion and proposed others. The criteria retained were those validated by at least two-thirds of the experts. We then developed clinical decision trees (algorithms) for managing the four main indications for caesareans and derived the criteria for NMIC.

The NMIC criteria are presented in Table 1. For each indication, all the criteria are considered simultaneously. A caesarean is judged to be non-medically indicated when all the criteria are met or when they are not documented and no opposing medical indication is provided. The NMIC rate was calculated for each hospital. This rate is the proportion of NMICs among all the caesareans performed for the four indications during the same period.

**Table 1 Tab1:** Criteria for non-medically indicated caesareans ^a^

Previous caesarean section	Prolonged/obstructed labour
Pre-labour caesarean not indicated if ^a^: - One previous caesarean section with transversal scar - Singleton foetus in cephalic presentation - Lack of ultrasound or clinical evidence of macrosomia - Lack of radiographic or clinical evidence of restricted pelvis - Possibility of performing emergency intra-partum caesarean section 24 h on call Caesarean during labour not indicated if ^a^: - Same criteria as pre-labour caesarean (see above) - Cervical dilation progressing normally (>2 cm in 4 h) - Presentation progressing normally at full dilation (no arrest >3 h) - Lack of evidence of foetal distress^b^ - No documented signs of uterine rupture OR Duration between full dilation and decision for caesarean delivery >3 h and no attempt of instrumental delivery (forceps or vacuum) if this is indicated	Pre-labour caesarean for presumed obstructed labour not indicated if ^a^: - Singleton foetus in cephalic presentation - Lack of ultrasound or clinical evidence for macrosomia - Lack of radiographic or clinical evidence of restricted pelvis - No documented history of fistula or uterine malformation - No documented history of uterine rupture Caesarean for failed induction or slow dilation without foetal distress is not indicated if ^a^: - Membranes intact OR - Membranes ruptured, uterine contractions adequate and time elapsed since stagnation of dilation under 4 h OR - Membranes ruptured, uterine contractions inadequate, no attempt at augmentation with oxytocin OR - Membranes ruptured, uterine contractions inadequate, augmentation with oxytocin and time elapsed since stagnation of dilation under 6 h Caesarean at full cervical dilation without foetal distress not indicated if ^a^: - Non-engagement of presentation and time elapsed between full dilation and decision for caesarean under 3 h - Engaged head and instrumental delivery (forceps or vacuum) not attemped
Pre-eclampsia	Foetal distress
Pre-labour caesarean not indicated if ^a^: - Lack of evidence of foetal distress^b^ - Lack of clinical or ultrasound evidence of foetal growth restriction - No documented signs of severity for the woman^c^ - No documented signs of abruptio placentae Caesarean during labour not indicated if ^a^: - Same criteria as pre-labour caesarean (see above) - Cervical dilation progressing normally (>2 cm in 4 h) - Presentation progressing normally at full dilation (no arrest >3 h)	Caesarean during labour not indicated if ^a^:signs of abruptio placentae - Clear amniotic fluid or not documented -No maternal fever or not documented - Cervix dilation or presentation progressing normally - Foetal heart rate normal (120–160 beats/min.) OR abnormal but uncorrected (oxygen administration and mother on left side)

^a^All criteria are required

^b^Signs of foetal distress: foetal heart rate abnormalities (<120 or >160 beats/min. or repeated decelerations); coloured amniotic fluid

^c^Signs of severe pre-eclampsia: blood pressure ≥160/110 mmHg; albuminuria ≥3+ or ≥3 g/24 h; oliguria <30 mL/h; headache; epigastric pain; vision disorders; neurologic disorders; seizures; hemolysis; low platelet count; high liver enzymes

Secondary assessment criteria are:
*Ratio of pre-/post-labour caesareans*
Caesareans fall into three groups: 1) those planned and performed before labour; 2) urgent caesareans performed before labour; and 3) urgent caesareans performed during labour. It is expected that improvements in intrapartum care quality would be accompanied by a decrease in urgent caesareans during labour and an increase in pre-labour caesareans—hence, a reduction in the ratio of pre-/post-labour caesareans [71].

*Health professionals’ knowledge score*
We developed short case histories (vignettes) to measure health professionals’ knowledge in terms of their ability to correctly apply the main indications for caesareans: previous caesarean, pre-eclampsia, prolonged/obstructed labour, foetal distress. These knowledge/skills criteria were based on the diagnostic reasoning criteria for indications as selected by the experts. Each professional’s knowledge score corresponds to the number of correct responses for the 33 vignettes.

*Caesarean quality score*
In addition to the diagnostic reasoning criteria for caesarean indications, the expert committee also developed good-practice criteria to assess whether the caesarean was performed at the proper time and appropriately. Those criteria are presented in Table 2.

**Table 2 Tab2:** Caesarean quality criteria

ᅟ	ᅟ
− Patient must be given clear information on the indication for the caesarean. − Elapsed time between decision and incision must be no longer than 30 min. − Preference is given to using local or regional anaesthesia. − Patient receives prophylactic antibiotics. − Misgav Ladach surgical technique is used. − Joel-Cohen skin incision is used. − Delivery is done using controlled cord traction rather than manually. − In post-operative care, patients without complications resume liquid diet after 6 h. − In post-operative care, high-risk patients (morbid obesity, pre-eclampsia, history of thromboembolism) undergo thromboembolism prevention therapy.	In each hospital, all caesareans performed over the same given period will be evaluated. One point will be attributed for each criterion met (0 for those not met). For each case, total points attributed will be divided by the total number of criteria, giving a score of between 0 and 100 %. Each hospital’s quality score will be the average of the scores for all the caesareans evaluated for that hospital.

*Resource availability score*
Resource availability indicators will be measured in each hospital before and after the intervention through a systematic and standardized inventory of available resources. For each facility, a hospital environment complexity index will be calculated to reflect the availability of the different categories of resources needed to provide good-quality obstetric care [72, 73]: basic services; screening tests; basic emergency obstetric resources; intrapartum care; general medicine services; anaesthesiology; human resources; teaching and clinical resources; and clinical care protocols.

*Perinatal mortality in infants delivered by caesarean*
We selected this indicator because we believe improvements to obstetric care prompted by audits should also have an impact on perinatal outcomes related to intrapartum care [65, 73]. Included in the definition are immediate neonatal deaths (within 24 h after birth) and fresh stillbirths; excluded are macerated stillbirths, deaths of premature infants (less than 37 weeks amenorrhea), and deaths of severely deformed infants. Perinatal mortality related to intrapartum care is defined as the number of immediate deaths and fresh stillbirths divided by the number of non-preterm caesarean deliveries in the same period.

*Intra-hospital maternal mortality among patients with caesareans*
This indicator was selected because we believe that, as in perinatal deaths, improvements in caesarean practice prompted by audits should also have a positive impact on maternal outcomes [73–75]. This indicator is defined as the ratio between the number of post-caesarean maternal deaths occurring in a hospital during the study period and the number of caesareans performed in that hospital over that period.

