**Fig. 1 Fig1:**
[figure not shown]
show the logic of the intervention

The intervention will begin with the training of local trainers on: 1) evidence-based standards for the management of labour, the reasoning used to diagnose the main indications for caesareans, and the quality of the surgical procedure; and 2) conducting clinical audits of indications for caesareans based on objective criteria (criteria-based clinical audits, CBCA). The trainers will create CBCA teams in their own hospitals and will organize training for obstetric teams on best practices. With a view to sustainability, no financial incentive will be given to local trainers or to health professionals who undergo the training in the intervention hospitals. Thereafter, decision-support reminders of evidence-based criteria for diagnosing the main indications for caesareans, conveyed via SMS, will be used to supplement the staff training.

The intervention consists of five stages:
*Training the trainers:* The local trainers are the chiefs of maternity services in the intervention hospitals (one physician per hospital). In May 2015, the trainers attended a 3-day training session led by two experts from the Society of Gynaecologists and Obstetricians of Burkina (SOGOB). The training was based on the WHO guidelines for managing complications of pregnancy and childbirth [43] and clinical decision algorithms that had been developed as part of this study (see Additional files 1, 2, 3, 4, 5 and 6). The session included 2 days of training on: 1) the diagnostic reasoning involved in identifying the main indications for caesareans (previous caesarean, prolonged/obstructed labour, pre-eclampsia/eclampsia, foetal distress); 2) the quality of the surgical procedure; and 3) the decision algorithms validated by the experts. A third day was allocated to training on conducting CBCAs.
*Establishing and training a multidisciplinary audit committee in each intervention hospital:* Setting up these CBCA committees (consisting of physicians, midwives, nurses, and administrators) will involve: a) identifying and training people who will be responsible for collecting data on caesareans; and b) training committee members on how to conduct CBCAs.

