### Data collection and processing

A data collection system has been set up in each of the 22 participating hospitals. This system is inspired by the WHO global survey on maternal and perinatal health [73], which considers both individual clinical data and organizational data at the health facility level. Information on the first 100 caesareans performed in the 6-month pre-intervention period and the first 100 performed in the 6-month post-intervention period in each hospital will be entered by local data collectors (midwives trained for this task). These midwives fill out a standard form for each eligible caesarean, which includes information on maternal characteristics, diagnosed complications, prenatal care, management of labour, caesarean indication and procedure, post-operative monitoring, and maternal and infant vital signs at discharge (see caesarean form in Additional file 11). This information will be obtained from hospital registers and from available medical records, whose quality and archiving are regularly monitored by the study coordinator. Data will be collected daily during both the pre- and post-intervention periods. With regard to organizational data and the knowledge evaluation questionnaire, the study coordinator will compile an inventory of the resources available in all the hospitals and will administer the questionnaires to health professionals before and after the intervention period.

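### Undocumented caesareans count as non-medically indicated, so any better record-keeping in the audited arm would lower the primary outcome without a change in practice

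*Protocol article*

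**What the plan says.** All references are to the protocol article.

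- **Outcome.** Assessment criteria: "The primary assessment criterion is the NMIC rate". On the denominator: "This rate is the proportion of NMICs among all the caesareans performed for the four indications during the same period".
- **Classification rule.** "A caesarean is judged to be non-medically indicated when all the criteria are met or when they are not documented". The second limb reads in full: "or when they are not documented and no opposing medical indication is provided". Several Table 1 entries work the same way: a sign with no entry is treated as absent.
- **Source.** Data collection and processing: "This information will be obtained from hospital registers and from available medical records". Trained midwives complete the trial form in all 22 hospitals, and the study coordinator monitors record quality in both arms.
- **Intervention arm.** Under Activities in the intervention group, hospitals set up criteria-based audits, with monthly meetings recommended. Setting up the audit committees includes "identifying and training people who will be responsible for collecting data on caesareans". Trainers are taught the study's decision algorithms, from which the non-medically indicated caesarean (NMIC) criteria were derived. Weekly text messages repeat the diagnostic reasoning. Control hospitals receive no intervention.
- **Checks.** Data quality control compares forms with source documents and defines a completeness rate for the forms.
- **Acknowledged limitation.** Potential limitations of the trial mentions only an effect of research data collection, taken to be similar in both arms.
- **Analysis.** Analysis strategy sets out a GEE on NMIC yes/no. It describes no separation of undocumented cases from cases with criteria documented as met.

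**The concern.** The numerator mixes two kinds of case: caesareans that the record shows were not indicated, and caesareans for which the record is silent. Only the first kind measures practice directly. The second also depends on how fully staff write notes, and the intervention works on those same items in one arm only.

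Staff whose caesareans are audited against a list have a reason to record the items on it. If they do so more than control staff, the odds ratio moves in the intervention's favour even where the decision to operate has not changed. The trial's main hypothesis concerns fewer unnecessary caesareans. A fall in the composite could not be read that way without knowing how much of it came from the silent records.

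**Working it through.** **1. Direction.** Take a case that is in the numerator through the undocumented limb and suppose the notes improve, with accurate entries.

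| New entry in the record | Class before | Class after |
|---|---|---|
| Finding that supports the caesarean | NMIC | not NMIC |
| All criteria recorded as met | NMIC | NMIC |

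No entry adds a case, so for this group better notes can only lower the measured rate. The condition about an opposing indication narrows the group but does not close the gap, because an opposing indication must itself be written down to count.

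**2. Reach of the checks.** Form-to-source comparison finds what the record holds and the form lacks. It cannot find what the record never held. Record monitoring covers both arms, but it does not offset an added stimulus in one.

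**3. Size.** The article does not give the undocumented share, so these inputs are assumed:
- s = share of counted NMICs that are truly indicated but undocumented;
- f = fraction of those newly documented, in the intervention arm only.

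Relative fall with practice unchanged = s × f. With f = 0.5:
- s = 0.10: 0.10 × 0.5 = 5%
- s = 0.25: 0.25 × 0.5 = 12.5%
- s = 0.50: 0.50 × 0.5 = 25%

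**4. Effect on the test.** Sample size calculation gives 22 hospitals, 100 caesareans each and ICC 0.02. The variance inflation factor is 1 + (100 − 1) × 0.02 = 2.98, which agrees with the stated 3. The effective number per arm is 1,100/3 ≈ 367. Base rates of 12% and 24% are the ends of the range in Background; the sample-size section states none.

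Chance of a significant result favouring the intervention = Φ[(d − 1.96·se0)/se1], where d is the difference in rates, se0 the pooled standard error and se1 the unpooled one. For 24% against 18%: d = 0.06, se0 = √(0.21 × 0.79 × 2/367) = 0.0301, se1 = √[(0.24 × 0.76 + 0.18 × 0.82)/367] = 0.0300, giving Φ(0.03) ≈ 51%.

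| s (f = 0.5) | Base 12%: rate, OR, chance | Base 24%: rate, OR, chance |
|---|---|---|
| 0.10 | 11.4%, 0.94, 4% | 22.8%, 0.94, 6% |
| 0.25 | 10.5%, 0.86, 9% | 21.0%, 0.84, 16% |
| 0.50 | 9.0%, 0.73, 26% | 18.0%, 0.70, 51% |

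With no bias the chance in this direction is 2.5%. These figures are approximate: 1,100 per arm counts all caesareans, whereas the outcome uses only the four indications (76% before the intervention).

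**5. What the companion measure would show.** Assumed example: the control rate is 12% documented plus 12% undocumented, and half of the latter is truly non-indicated, so the true rate is 12 + 6 = 18%. The intervention halves this to 9% and everything is documented.
- Composite: 24% to 9%, a fall of 15 points.
- True rate: 18% to 9%, a fall of 9 points.
- Documented NMIC: 12% to 9%, a fall of 3 points.

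The composite overstates the practice effect and the documented class understates it. By the formula in step 4, power for 12% against 9% is about 26%.

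**The case against.** Five points can fairly be made on the other side.

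- **Better records are an inference.** No passage says that the intervention improves notes. Audits and reminders finish with the intervention in April 2016, and the outcome is measured in the following six months, so the habit would have to persist. This stands: differential improvement is plausible, not established.
- **The rule is narrower than it may look.** A case with missing criteria and a recorded opposing indication is not counted. This stands, and it reduces the pool at risk.
- **Data collectors.** A reader might infer that intervention hospitals have additional trial data collectors. The article does not support that. Those people serve the audit committees; trial data come from trained midwives in all 22 hospitals.
- **Safeguards exist in both arms.** Record monitoring and a form completeness rate are planned. They may reduce the amount of silence in the records, but they do not show whether it changes differently by arm.
- **Table 1.** Footnote a, "All criteria are required", sits on lists joined by OR, and the full-dilation list pairs a non-engaged presentation with "Engaged head and instrumental delivery (forceps or vacuum) not attemped". A reader might infer that this last category can never be NMIC. The OR branches read naturally as alternatives, and the full-dilation layout may be damaged by text extraction, so only a request for clarification remains.

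A stricter remedy, allowing a claim only if documented NMIC also falls significantly, is open to the objection in step 5 of the working: a true halving could fail that test about three times in four.

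**Conclusion.** The concern holds as a weakness in how the primary outcome is defined. Undocumented cases without a recorded opposing indication enter the numerator, the arms differ in their stimulus to document these criteria, and the article describes no analysis that would reveal the consequence. The bias, if present, favours the intervention.

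Its size is unknown. On assumed shares of 10-50% with half newly documented, it is a 5-25% relative fall: minor at the low end, and enough at the high end to give a 26-51% chance of a significant result with no change in practice. These figures assume accurate new entries, no improvement in control records, and carry-over beyond the end of the activities.

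A reader might infer that documentation alone could deliver the whole 50% target. That needs half of all counted cases to be truly indicated but undocumented, and every one of them to become documented (0.5 × 1 = 50%). Nothing in the article supports that combination.

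**What to change.** 1. Code every four-indication caesarean by algorithm, from data already on the form, as documented NMIC, documented indicated, or not documented.
2. Keep the current composite as the primary outcome.
3. Pre-specify a companion GEE on documented NMIC with the same denominator. State that it is biased against the intervention, so that the two results bracket the practice effect. Give risk differences beside the odds ratios: with accurate entries the bracket is exact for absolute differences and only approximate for odds ratios.
4. Report the not-documented proportion by arm and period. The pre-intervention share can be computed from the data already collected.
5. Interpret a fall in the composite as a change in practice in the light of items 3 and 4. Do not make significance on documented NMIC a condition.
6. As a minor point, reconcile the Table 1 footnote with the OR-joined lists and the full-dilation list before post-intervention coding.

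The cost is one more code per record and one more model, with no new data collection, and a more cautious conclusion if the two results diverge.

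### Table 1, the classifier for the primary endpoint, contradicts its own all-criteria rule: the full-dilation block lists two mutually exclusive lines without OR, and the scope of the OR in the previous-caesarean block is undefined

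*Protocol article*

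**What the plan says.** The Assessment criteria section of the protocol article makes the NMIC rate the primary criterion. Its denominator is all caesareans done for the four main indications, and Table 1 decides which of them count as NMIC. These statements govern how the table is read:

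- **Text before the table.** "For each indication, all the criteria are considered simultaneously". Then: "A caesarean is judged to be non-medically indicated when all the criteria are met or when they are not documented", provided the record shows no contrary medical indication.
- **Footnote a**, attached to the table title and to each block heading: "All criteria are required".
- **Full-dilation block, prolonged/obstructed labour.** The heading is "Caesarean at full cervical dilation without foetal distress not indicated if" and carries footnote a. Two lines follow with no connecting word: "Non-engagement of presentation and time elapsed between full dilation and decision for caesarean under 3 h - Engaged head and instrumental delivery", where the second line goes on to say that forceps or vacuum was not tried.
- **Slow-dilation block, directly above in the same cell.** It also carries footnote a, but its four lines are joined by three printed ORs.
- **Previous caesarean, during labour.** A list of required criteria ends with "No documented signs of uterine rupture OR Duration between full dilation and decision for caesarean delivery >3 h and no attempt of instrumental delivery", with no sign of how far back the OR reaches.

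**The concern.** A classifier for a primary endpoint should give one answer for one record. Here the combination rule and the full-dilation block cannot both be followed. If a coder or programmer applies the rule literally, a fully documented caesarean in that block can never be NMIC, yet it still counts in the denominator. The block would then be unable to show any change in decisions at full dilation, and the NMIC rate would be too low. Such a case could count only through the clause on undocumented criteria, so in this block the classification would depend on record-keeping rather than on the decision taken.

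The previous-caesarean block has a different and lesser fault. It does print an OR, but two careful readers can bracket it differently and disagree on the same woman.

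**Working it through.** **Full-dilation block.** The document states no figure to reproduce, so the check is one of logic. Let E = head engaged, T = under 3 h from full dilation to decision, I = instrumental delivery attempted.

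- Line 1 = (not E) and T
- Line 2 = E and (not I)
- Rule as printed: Line 1 AND Line 2. This needs both not-E and E, so it is never true.
- Rule if the lines are alternatives: Line 1 OR Line 2.

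All 8 fully documented combinations:

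| E | T | I | AND (as printed) | OR (alternatives) |
|---|---|---|---|---|
| no | no | no | not NMIC | not NMIC |
| no | no | yes | not NMIC | not NMIC |
| no | yes | no | not NMIC | NMIC |
| no | yes | yes | not NMIC | NMIC |
| yes | no | no | not NMIC | NMIC |
| yes | no | yes | not NMIC | not NMIC |
| yes | yes | no | not NMIC | NMIC |
| yes | yes | yes | not NMIC | not NMIC |

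The result is 0 of 8 under AND and 4 of 8 under OR. These are counts of logical combinations, not proportions of patients.

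**Effect on the rate.** Let d be the share of four-indication caesareans that are fully documented cases in this block, and m the proportion of those that satisfy one of the two lines. The literal rule lowers the NMIC rate by d × m compared with the alternatives reading. The article gives neither d nor m.

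**Does footnote a hold elsewhere?** In the slow-dilation block the printed alternatives are also exclusive (membranes intact or ruptured; contractions adequate or inadequate). Requiring every line there would also leave nothing, so footnote a cannot mean every listed line in that block. It can only mean every element within one alternative.

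**Previous-caesarean block.** Let C be the required criteria before the rupture line (the pre-labour set, normal dilation, no arrest above 3 h at full dilation, no foetal distress), U = no documented rupture signs, and X = the branch after the OR.

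- Reading A, OR joins only the last line: C and (U or X).
- Reading B, OR joins the whole block: (C and U) or X.

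Take a woman with arrest above 3 h at full dilation before the decision, and no instrumental attempt although one was indicated, with everything else in C and U met. X holds and C fails. Reading A gives not NMIC and reading B gives NMIC. Reading A also sets the branch for more than 3 h beside a required absence of arrest above 3 h. Under reading B the second branch drops the single-scar, foetal-distress and rupture conditions.

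**The case against.** The strongest reply is that this is a drafting slip with only one workable reading. Footnote a already cannot be literal in the slow-dilation block, so a sensible coder would treat the two full-dilation lines as two scenarios. That stands, and it makes alternatives the probable intention. It does not remove the inconsistency, because the table marks alternatives with OR in one block and omits it in the next, under the same footnote and the same text.

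The article also says that the NMIC criteria were derived from decision algorithms, which are placed in additional files not shown here and may state the branch on engagement correctly. Hospital NMIC rates had already been calculated for the baseline period, so some logic was already in use. An OR lost when the table was converted from PDF to text cannot be wholly excluded either: the foetal-distress cell looks damaged, although the neighbouring ORs survived. These points stand as limits on the finding.

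Finally, any literal rule would apply to both arms and both periods, so it is not by itself differential. That is fair. Only if documentation changed differently between arms could the undocumented-criteria clause act unevenly, and nothing in the article shows that it did.

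**Conclusion.** The point holds as an internal inconsistency in the published definition of the primary endpoint. The text, footnote a and the full-dilation block cannot all be followed: as printed, no fully documented case in that block can be NMIC. This needs no assumption beyond a head not being both engaged and unengaged at the decision. The undefined OR in the previous-caesarean block is a separate, lesser ambiguity, and the mutual-exclusion argument does not extend to it.

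A reader might infer more than the article supports in two ways:

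- **That full-dilation cases were in fact scored as zero.** Nothing shows how records were coded, and alternatives are the likely intention.
- **That the NMIC rate is understated by some number of percentage points.** Any such figure needs guesses for d and m that have no basis in the article. Setting it against the 12 to 24 % quoted in the Background would also mix denominators, because that range refers to caesareans in the country and not to the trial's four-indication caesareans.

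The size of the effect on the NMIC rate is therefore unknown.

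**What to change.** Reconcile Table 1, footnote a and the combination rule in the text, leaving the clinical thresholds as they are:

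1. Write the table as explicit AND/OR logic. Mark the two full-dilation lines as alternatives, and limit footnote a to all criteria within an alternative.
2. Bracket the OR in the previous-caesarean, during-labour block. Have the existing expert panel state which shared conditions apply to its second branch.
3. Confirm which logic produced the baseline NMIC rates, and check it against the algorithms in the additional files.
4. Apply one coded algorithm to the pre- and post-intervention records before any comparison by arm.

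The cost is a table correction and, if the logic differs from what was used, a re-run of the classification on data already on the caesarean form. No new data are needed. The downside is that the reported baseline NMIC rate may shift slightly.
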